# 1 Study overview

A major goal in the neurological rehabilitation of patients with severe disorders of consciousness is to enhance the arousal and ability of these patients to communicate.

To activate them and thus enhance their state of consciousness, patients are treated with multimodal stimulation. This stimulation consists of vestibular, auditory, tactile, olfactory, and visual inputs. To stimulate vestibular sensory information it appears to be essential to mobilize the patient into a vertical position. Although desirable, head-up tilt cannot always be easily realized in the early stages after brain injury when patients are still unconscious. A common problem is the occurrence of syncope due to central sympathetic dysfunction and the absence of the venous pump as a result of paralysis of the leg muscles.

In the past, head-up tilt was performed gradually over a period of several weeks, in order to stabilize the patient's circulatory system and prevent recurrent syncope. In clinical practice this is done with a tilt table. The Erigo is a tilt table with an integrated robotic stepping device, which was developed to combine the advantages of a classical tilt-table therapy with those of a passive-movement therapy.. It provides a feasible way of simultaneously inducing passive leg movements and gradually inclined head-up tilt in patients who are comatose or semi-comatose. Moreover, it was shown that patients with a traumatic spinal cord injury with similar vegetative dysfunctions could be mobilized faster by using such a device.

The aim of this study is to determine, if an Erigo therapy has an immediate stabilizing effect on the cardiovascular system and if it increases vigilance in the early stages of mobilization of patients with a severe brain injury. These effects will be compared with a standard tilt-table therapy.

Vegetative functions will be determined by measuring blood pressure and recording heart rate before, during, and after the intervention. Reactions on the Erigo will be compared with those of the standard tilt table. In addition, vigilance will be measured by means of the Coma Recovery Scale-revised.

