#### 4.2.2 Secondary outcome measure

To evaluate an immediate stabilizing effect of the Erigo therapy on circulation, the following cardiovascular parameters will be measured:

- Heart rate
- Blood pressure; the Hypothesis: difference between initial value and the value after the intervention phase is greater for the tilt-table therapy (drop in blood pressure during tilt-table therapy)
- Oxygen saturation; the Hypothesis: increased oxygen saturation during Erigo therapy
- As co-variables the duration of verticalization (max. of 30 min per therapy session), and the degree of the maximum tilt will be analyzed

To evaluate a clinically unapparent effect on vigilance the following parameters will be measured:

- Skin conductance as reaction to command (should increase during Erigo therapy)
- Heart rate variability (should increase during Erigo therapy)
- Head control/movement during therapy (better during Erigo therapy)

The change in muscle tone or spasticity will be measured before the intervention, after the intervention, and after a 3 week follow-up period using the

- Ashworth-Scala.

To better compare the results of this study with results of international studies, the following parameters will be measured:

- at study onset: GCS (Glasgow Coma Scale)
- at discharge: GOS (Glasgow Outcome Scale)

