## 7 Study procedure

### 7.1 Procedure

| Erigo                                                                                                                                                                                           | Tilt table |
|-------------------------------------------------------------------------------------------------------------------------------------------------------------------------------------------------|------------|
| Attachment of ECG electrodes, blood pressure cuff, and pulsoxymeter for continuous measurement of pulse, ECG, blood pressure, and oxygen saturation; also for performance of first measurement. |            |
| Patient is transferred from bed/wheelchair to the Erigo or to the tilt table, is attached to it, and secured with a belt over the stomach.                                                      |            |

|                                                                                                                                                                                                                                                                                                |  |
|------------------------------------------------------------------------------------------------------------------------------------------------------------------------------------------------------------------------------------------------------------------------------------------------|--|
| The foot supports are adjusted to the individual length of the legs of the patients.                                                                                                                                                                                                           |  |
| Adjustment of range of leg movement to patient's maximally possible range.                                                                                                                                                                                                                     |  |
| Start of leg drive at a maximally tolerated speed (the goal is 40 steps/min or at least 20 steps/min) while patient remains in horizontal position.                                                                                                                                            |  |

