| Upright placement to 30 degrees; conditions maintained for about 5 min.                                                                                                                                                                                                                        |  |
| Subsequently the patient is uprighted to 50 degrees (if appropriate, with same drive parameters); if circulation is good, to 70 degrees.                                                                                                                                                       |  |
| At least 15-min-long or maximally 30-min-long therapy during the achieved angle of verticality. The duration of mobilization in the indicated time period is as long as possible, if there is no depression of the circulation and in agreement with the predetermined criteria (see below).   |  |
| At the end of therapy the Erigo or tilt table is lowered into the initial horizontal position by about 15 degrees, with a break for the patient to acclimatize him/herself. After the final measurement the apparatus is disassembled and the patient is transferred to the bed or wheelchair. |  |

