## **10 Termination criteria**

Individual

- If the systolic blood pressure falls by 20 mmHg or the diastolic blood pressure by more than 10 mmHg during the uprighting of the patient, therapy is continued at the next lowest tolerated angle of uprightness (30 or 50 degrees).
- The same procedure is followed with symptoms of a presyncope (tachypnoe, paleness, increased sweating...).
- Therapy is immediately terminated if the pulse falls below 40 beats/min or rises above 140 beats/min.
- Arterial hypotension (<80 mmHg).
- The occurrence of a new disease or complication of the primary illness that makes a continuation of the study impossible.
- Legal proxy withdraws participation agreement.

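### Section 4.2.2 names duration of verticalization and maximum tilt as co-variables for the circulation outcomes, yet both are set after randomisation by circulatory tolerance, so adjusting for them would bias the device comparison

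*Protocol*

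**What the plan says.** Section 4.2.2 of the protocol introduces its first block of secondary outcomes for the randomised trial with "To evaluate an immediate stabilizing effect of the Erigo therapy on circulation, the following cardiovascular parameters will be measured". It lists heart rate, blood pressure (hypothesis: a larger drop on the tilt table) and oxygen saturation. The last bullet of the block reads "As co-variables the duration of verticalization (max. of 30 min per therapy session), and the degree of the maximum tilt will be analyzed".

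Section 7.1 describes how a session runs. Every patient first gets "Upright placement to 30 degrees; conditions maintained for about 5 min". The table then goes to 50 degrees and, "if circulation is good, to 70 degrees". The achieved angle is kept for 15 to 30 minutes: "The duration of mobilization in the indicated time period is as long as possible, if there is no depression of the circulation".

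Section 10 adds the step-down rule. If systolic pressure falls by 20 mmHg, diastolic pressure falls by more than 10 mmHg, or presyncope appears, "therapy is continued at the next lowest tolerated angle of uprightness (30 or 50 degrees").

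Section 1 makes circulation a study aim: "The aim of this study is to determine, if an Erigo therapy has an immediate stabilizing effect on the cardiovascular system". Section 6.2.2 gives an analysis for the primary outcome, CRS-R, and none for the circulation outcomes.

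**The concern.** A covariate is safe to adjust for when the treatment cannot have changed it, as with a baseline measurement. Duration and maximum tilt are not of that kind. Both are determined after randomisation, on the assigned device, by how well the circulation holds up, which is what the Erigo is meant to improve. Section 4.1, writing of the pilot, names longer and steeper mobilization as the expected benefit.

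Tilt has a second problem: it is set partly by blood pressure, one of the outcomes. A patient held at 50 degrees is often there because pressure fell at 70. Comparing arms among patients with the same held angle and session length therefore compares patients who have been partly matched on the outcome.

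At stake is the trial's answer on circulatory stabilization. A real benefit could be understated, or a difference could appear for reasons unrelated to blood pressure.

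**Working it through.** **Where the variables come from.** Maximum tilt depends on good circulation at each step (7.1) and on the pressure and presyncope triggers (10). Duration depends on there being no circulatory depression (7.1). Both follow randomisation and both respond to the device. The 30-degree step does not have this problem, because 7.1 sets it for every session before any decision on tolerance.

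**The plan's own figure.** The only stated sample size is for CRS: n = 2 × (1.96 + 0.84)² × 3.5² / 3² = 2 × 7.84 × 12.25 / 9 = 21.3, so 22 per group; 22 / 0.9 = 24.4, so 25. It reproduces, and this point does not depend on it. The protocol gives no effect or spread for blood pressure, so every mmHg input below is an assumption.

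**Model.** Systolic fall at 70 degrees: F = patient mean N(μ, sdP) + session noise N(0, sdS). Fall at angle a: F × sin(a)/sin(70°). The table goes 30, 50, 70 degrees; a fall of 20 mmHg or more returns the patient one step, with 30 degrees the lowest. There are 22 patients per arm and 9 sessions each, the measurement count in section 7.5. Arms are compared on patient means, by t-test unadjusted and by ANCOVA adjusted for held angle. The share of sessions stepped down is 1 − Φ((20 − μ)/√(sdP² + sdS²)); for μ = 15 and SDs 8 and 6 this is 1 − Φ(5/10) = 31%.

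| Mean fall, tilt table v Erigo | sdP, sdS | Tilt-table sessions stepped down | Unadjusted difference (mmHg) | Adjusted for held angle | Share lost |
|---|---|---|---|---|---|
| 8 v 3 | 4, 3 | 1% | 5.0 | 4.7 | 6% |
| 10 v 5 | 4, 3 | 2% | 4.9 | 4.4 | 10% |
| 10 v 5 | 6, 4 | 8% | 4.5 | 3.5 | 22% |
| 15 v 5 | 8, 6 | 31% | 7.5 | 4.6 | 39% |
| 20 v 10 | 10, 8 | 50% | 6.0 | 2.0 | 67% |
| 25 v 15 | 12, 10 | 63% | 5.4 | 0.9 | 83% |

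The share lost is (unadjusted − adjusted)/unadjusted, for example (5.4 − 0.9)/5.4 = 83%. In the first three rows power goes from 98% to 97%, 99% to 96% and 73% to 56%. Over all nine combinations of the larger falls (15 v 5, 20 v 10, 25 v 15) and the three larger SD pairs, power is 68–96% unadjusted and 6–69% adjusted. With 25 patients and 12 sessions per arm the differences are almost the same (4.3–7.6 against 0.9–4.6 mmHg).

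**Does it depend on which reading is used?** Section 7.1 provides "for continuous measurement of pulse, ECG, blood pressure, and oxygen saturation", so several readings are possible. Over the same nine combinations:

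| Reading | Unadjusted (mmHg) | Adjusted for held angle |
|---|---|---|
| At the held angle | 4.4–7.6 | 1.0–4.6 |
| Session peak | 6.5–9.1 | 0.9–4.6 |
| 30-degree step (true value 10 × 0.5/0.94 = 5.3) | 5.25–5.45 | 0.5–2.4 |
| Back at horizontal, 30% of the fall persisting | 3.0–3.1 | 0.3–1.4 |

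**Adding duration.** Adjusting for held angle and duration leaves 0.5–1.7 mmHg. This is partly built in, because duration was generated as 33 − 0.6 × held fall + N(0, 4), limited to 15–30 minutes. It shows what happens if session length follows pressure closely.

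**A differently built model.** Device effects of 3, 5 or 8 mmHg and angle slopes of 0 to 6 mmHg per 10 degrees give 12 scenarios, all with attenuation. Tilt alone removed from 9% (4.85 to 4.39) to 55% (2.91 to 1.32). Tilt and duration together removed about 53–78%, again with duration generated from the fall.

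**The case against.** The strongest objection is that the protocol states no adjustment. The bullet says the two variables will be analyzed, stands in a list of measured parameters under a secondary-outcome heading, and names no model. It could mean accompanying description, and details of secondary models are commonly left to the SAP. This limits the point: a reader might infer that a biased adjusted analysis is already fixed, and the text does not support that. What stands is that co-variable ordinarily means adjustment and nothing in the protocol restricts it. The protocol has assigned a role, and an SAP that followed it would carry the bias forward.

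A reader might also infer that tolerance will be neither compared nor reported between arms. The protocol does not say so, and nothing in it prevents that comparison.

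The size objection is fair. Large losses need large falls, with roughly a third to nearly two thirds of tilt-table sessions stepped down. With rare step-downs, adjusting for tilt costs little.

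The direction is not universal. With falls of 12 v 7 mmHg and mostly non-pressure step-downs (60% v 10%), adjusting for tilt moved the estimate from about 3.8 to 4.0–4.3, depending on programming, which is nearer the true 5. With no true pressure difference and non-pressure step-downs of 25% v 5%, adjusting for tilt gave a spurious difference of 1.7–2.0 mmHg favouring the tilt table, significant in 23–30% of runs. With duration added, that shrank to 0.4 mmHg and 7%.

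Finally, the unadjusted held-angle reading is not clean either: it returns 4.4–7.6 of a true 10 mmHg, because the arms are read at different angles. Wanting tilt and duration beside blood pressure is reasonable, but adjusting for them does not repair this. The 30-degree reading does give an equal-tilt comparison, though of a different quantity.

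**Conclusion.** The point holds for the secondary circulation outcomes and is conditional: if blood pressure, heart rate or oxygen saturation are adjusted for duration or maximum tilt, the device comparison is biased. Because section 10 lowers the angle when pressure falls, the expected direction is towards no difference. For adjustment by tilt, the loss runs from slight (6–10% of the difference at 1–2% step-downs) to more than half (67–83% at 50–63%). These figures rest wholly on assumed falls and spreads and cover blood pressure only. Other causal structures could move the estimate differently, so a reader should not infer that a real benefit would always be hidden. The primary CRS-R analysis names neither variable and is unaffected.

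Nor does the step-down rule by itself call for an event outcome. In the nine larger-fall combinations, step-down events had power of 62–95%, much like unadjusted blood pressure.

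**What to change.** Reword the last bullet of the circulation block in 4.2.2. Make duration of verticalization and maximum tilt (recorded as the highest angle held) secondary outcomes, averaged per patient and compared between arms as randomised. State that blood pressure, heart rate and oxygen saturation are not adjusted for them. If a comparison at equal tilt is wanted, use the reading in the 30-degree step of section 7.1.

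In the nine larger-fall combinations, the two variables are informative as outcomes: held angle is 7–15 degrees lower on the tilt table (power 61–96%) and duration 1.8–2.4 minutes shorter (61–93%), or 0.6–0.8 minutes (29–54%) if only weakly tied to the fall. If step-downs are rare, the angle will differ little.

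The cost is one reworded bullet. Both variables are already to be analyzed, and the sample size and section 10 triggers do not change. The downsides are additional secondary outcomes and, if the 30-degree reading is used, a weaker orthostatic stimulus and hence a different estimand.

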## 5 Medical device

### 5.1 General description

Together with employees from the Orthopedic University Clinic Heidelberg and the Paraplegic Center in Balgrist (Zürich, Switzerland), a working group developed a so-called rehabilitation-stepper in order to combine the advantages of the classical standing board training with a simple to perform movement therapy. The relevant drive and positioning devices for the legs were integrated into a commercially available standing board, which is able to progressively adjust the degree of uprightness between lying and upright positions to the circulatory status of the patients. Thus, it is possible to move the legs in a way that corresponds to physiological walking (joint angle, phase-correct loading and unloading of the sole of the foot, speed). According to the latest neurophysiological findings, this type of movement provides a maximum trigger for activating the spinal gait pattern generators in the spinal cord and thus the muscles of the lower extremities ([7]).

(Photo removed for publication)

Figure 1: Erigo

## 5.2 Effects (therapeutic, diagnostic)

Potential Effects:

- Stabilization of the circulation – by improving the venous blood backflow to the heart by passive movement of the legs and activation of the muscles as a result of the triggering of the spinal gait program
- Improvement of vigilance – by simultaneously applying two forms of activation out of the coma stimulation

Additional expected therapy effects on secondary consequences of a long immobilization due to a severe quantitative disturbance of consciousness:

Osteoporosis prophylaxis – by means of phase-correct loading and unloading of bony structures

- Thrombosis prophylaxis – by passive movement of the legs and uprighting of the body
- Pneumonia prophylaxis – by increasing the intrathoracic gas volume by lowering the diaphragm during the upright positioning
- Contracture prophylaxis – by passive movement of the joint with adjusted speed
- Spasticity-reducing effect – through passive, reciprocal movement and activation of the spinal gait program

## 5.3 Adverse events, risks, and stress for study participants

- Under unfavorable conditions syncopes can occur during therapy on the Erigo. Possible risks include the loss of consciousness, prolonged bradycardia or hypotonia. However, we must point out that these orthostatic syncopes which occur in extreme cases can also occur in the transitional phase between lying and upright positioning during wheelchair mobilization, which takes place anyway, and the alternative tilt-table therapy. Since the passive leg movement on the Erigo occurs at the same time as the increased backflow of venous blood to the heart, the risk of syncope is according to the latest study information less on the Erigo than on the tilt table [6]). The remaining risks correspond to those of a typical physiotherapeutic treatment and thus are identical to those in the study and the control group. They are not increased by participation in a study compared to the usual therapy.

## 6 Study design/ Type of study

The pilot study is a prospective, monocenter, randomized study with a cross-over design. Each of the 20 participants will receive one therapy session on the Erigo and one on the tilt table. The time between the therapy sessions will last at least 1, maximally 7 days. The order of the type of treatment will be randomized.

The main study will be prospective, monocenter, controlled, and randomized. The main aim - to measure the improvement in vigilance on the Coma Recovery Scale – will be carried out by a blinded examiner. An experienced blinded examiner from the Neurological Clinic Bad Aibling will interpret the results. She will assess the data after their entry into a database, pseudonymization and randomized assignment to an intervention group. Depending on their group, the patients will receive four therapy sessions per week on the Erigo or on the tilt table. The study is planned to last three weeks. Irrespectively the normal range of therapy for apallic and minimally responsive patients (e.g., activating care, physio-, Ergo and swallowing therapy as well as physical therapy) will be performed. All study patients will receive at least five additional sessions of individual therapy besides the Erigo or tilt-table therapy.

A follow-up examination is planned to take place 3 weeks after the end of therapy. In the three weeks between therapy end and the follow-up examination the patient will be mobilized by means of the classical physiotherapy, not with the Erigo or the tilt table. .

## 6.1 Method of randomization

### 6.1.1 Pilot study

**Allocation procedure:** All patients will receive one therapy session on the Erigo and one therapy session on the tilt table. The sequence of both therapies will be applied in random order. Consequently, patients will be randomized in one of two groups (1 = tilt table - Erigo, 2 = Erigo – tilt table) by means of a computer-generated randomization list.

**Concealment:** The computer-generated randomization list will be prepared by the Department for Medical Data Evaluation of the Schön Kliniken. **Study procedure:** Each patient who meets the inclusion or exclusion criteria will be immediately and consecutively reported on to the statistician or his/her representative. He/she will inform those involved in the project about each consecutive test person's group within the fixed order (descending) by telephone or in person and will note the patient data (Surname, Name, Date of birth) on the randomization list. The first patient will receive the number 1, the second patient, the number two, and so on, and group allocation will be recorded. A log book will be kept on the assignments and will be available for inspection at the end of the study. In this way the secrecy of the as yet not applied randomization order is ensured. A drop-out will be substituted by the next test person in chronological order, but the assignment to therapy and control group will be kept the same as that of the drop-out.

Randomized controlled trial

**Allocation procedure:** The study participants will be assigned to one of two groups: **Group 1 = treatment with the tilt table, Group 2 = treatment with the Erigo.** The randomized stratified grouping is performed in accordance with two criteria, which are expected to have an effect on the outcome of the patients: the original diagnosis (traumatic vs. non-traumatic) and severity of the disorder of consciousness according to the CRS at study begin (apallic vs minimally responsive) ([9]).

**Non-disclosure conditions and study procedure** are the same as in the pilot study.

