### 6.2.2 Randomized controlled trial

Fifty patients will be enrolled in this study.

Sample size calculation

The sample size was estimated according to the main criterium measured by CRS and based on a 6-week follow-up on the effect of the standard therapy in 12 minimally responsive/apallic patients. The differential value of the CRS before and after a 6-week standard therapy showed a mean value improvement of 6.5 points with a variance of 12.3 (SD=3.5). An additional improvement of the CRS by 3 points is expected as results of the study planned here. This means that on the average an additional improvement in half of the evaluated items of the CRS is expected.

The sample size was estimated in order to check by inference statistical means the hypotheses of an interval-scaled feature ([10]) if the prerequisite of a corresponding normal distribution is fulfilled. The values  $\alpha = 5\%$  two-sided, power = 80% result in a group size of 22 patients for each of the two groups with the expected increase of CRS by 3 points. A difference of at least 3 points between the

two groups can be established as significant in case of a variance of the differential values (before/after treatment) of the CRS of  $3.5^2 = 12.3$  and in group size of  $n=22$  with an error probability of 0.5 and a power of 0.8. In addition the number of therapy drop-outs was so determined that the required number of patients will still be achieved even after subtracting an expected drop-out rate of 10%. Thus, a total of 25 patients as group size is included in the randomization procedure.

A 2-way analysis of variance (ANOVA) will be performed to statistically analyse the primary outcome parameter CRS-R. If the assumptions of homogeneity of variances or normal distribution are disproven, nonparametric tests will be used.

In case patients withdraw from the study at the wish of the caretaker, the patient will be referred to in the log book as “intention-to-treat”.

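### Replacing an RCT drop-out with the next patient in the same arm makes about 5 allocations known in advance and non-random, although the 25 per group already allows for drop-out

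*Protocol*

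**What the plan says.** Protocol section 6.1.1, in the pilot's study-procedure paragraph, describes a computer-generated list held by the statistician or a representative. For each new patient, "He/she will inform those involved in the project about each consecutive test person's group within the fixed order (descending) by telephone or in person". It concludes: "In this way the secrecy of the as yet not applied randomization order is ensured". The next sentence gives the replacement rule: a drop-out is "substituted by the next test person in chronological order, but the assignment to therapy and control group will be kept the same", so the newcomer takes the arm of the patient who left.

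The text on the randomized controlled trial follows under the same heading. It assigns patients to tilt table or Erigo, stratified by diagnosis (traumatic or non-traumatic) and severity (apallic or minimally responsive). It then says: "Non-disclosure conditions and study procedure are the same as in the pilot study". No exception is made for substitution.

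Section 6.2.2 enrols fifty patients. It sets 25 per group so that "the required number of patients will still be achieved even after subtracting an expected drop-out rate of 10" per cent. On withdrawals it says: "In case patients withdraw from the study at the wish of the caretaker, the patient will be referred to in the log book as", followed by the label intention-to-treat. The term appears nowhere else in the protocol.

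**The concern.** Concealment means that whoever brings a patient into the trial cannot know which arm comes next. Under the replacement rule, a drop-out announces the next arm. The trial has one centre, staff have been told the drop-out's group, and the two devices cannot be mistaken for each other. Only the CRS-R rater is blinded (sections 1, 4.2.1 and 6). So the arm of the substitute is known before enrolment and is set by an earlier patient's departure instead of by chance.

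Two further problems follow. The substitute is defined by time order, with no mention of stratum, although the strata were chosen because they are expected to affect outcome. And replacement makes good a loss for which the sample size already allows, which leaves the protocol inconsistent about how many patients it will enrol.

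No later analysis plan can restore concealment or randomise a slot that was filled by rule.

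**Working it through.** **Does the rule reach the RCT?** The rule stands in the paragraph labelled study procedure, and the RCT adopts the pilot's study procedure by that name. The rule's wording also speaks of a therapy and a control group. That fits the parallel-group trial; the pilot's two groups are treatment sequences.

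**The plan's own sample size.** Inputs from section 6.2.2: difference 3 points, SD 3.5, two-sided alpha 5%, power 80%, drop-out 10%. (The section also prints an error probability of 0.5, which is a separate inconsistency; the 5% figure is used here.)

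- Normal approximation: n = 2 x (1.960 + 0.842)² x 3.5² / 3² = 2 x 7.849 x 12.25 / 9 = 21.4, so 22 per group. This reproduces the plan. A t-based calculation gives 22.4, so 23.
- Drop-out allowance: 22 / 0.9 = 24.4, so 25 per group and 50 in total. This also reproduces.

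**Is replacement needed?**

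- Retained without replacement: 25 x 0.9 = 22.5 per group, against 22 required.
- In total: 44 / 0.9 = 48.9 randomised patients are enough for 44 completers, and 50 are planned.
- Power with 22 per group is 81.1% (normal) or 79.3% (t-test). With all 25 per group analysed at the same effect and SD it is 85.8% or 84.4%.

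The planned number is reached without any substitute.

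**How many allocations are affected?**

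- Expected drop-outs: 0.10 x 50 = 5, hence about 5 replacements and 50 + 5 = 55 enrolled.
- If substitutes also drop out at 10% and are replaced: 50 / 0.9 = 55.6, so about 56 enrolled. About 5.6 of these, or 10%, are allocated without randomisation.
- If 50 is instead a cap on enrolment, about 5 of the 50 are replacements and only about 45 are randomised.
- Chance that the rule is triggered at least once, taking drop-outs as independent: 1 - 0.9^50 = 99.5%.

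**Stratum match.** The protocol does not give the stratum mix. If the substitute's stratum is independent of the drop-out's, the chance of a match is the sum of the squared stratum shares. Three assumed mixes:

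| Assumed shares of the four strata | Chance of a match |
|---|---|
| 25/25/25/25% | 25% |
| 10/20/30/40% | 30% |
| 50/30/10/10% | 36% |

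Under these mixes, most substitutes would come from a different stratum.

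**The case against.** **The scale is small, and there are safeguards.** The rest of the list stays with the statistician, eligible patients are to be reported at once and in sequence, and the primary outcome is rated blind. The protocol does not say that the treating staff decide on enrolment. All this stands. It limits the opportunity for selection and confines the defect to the replacement slots. It does not make those slots random, and a blinded rater does not protect against selection at entry.

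**The next patient might be meant within stratum.** The text does not exclude this, so the effect on stratification is a possibility that the wording leaves open. The arm would still be known in advance.

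**A reader might infer that the trial becomes a completers' comparison.** The word substituted, the counting of the required number after drop-outs are subtracted, and the use of intention-to-treat only as a log-book label all point that way. But the protocol names no analysis set and does not say that replaced patients are excluded. The log-book sentence can also be read as marking withdrawals for retention, and an analysis plan not shown could keep them in.

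**A reader might also put a size on such a bias.** If 10% of one arm dropped out and would have gained 0 points instead of 6.5, leaving them out would raise that arm's mean by 0.10 x 6.5 = 0.65 points, or 0.65 / 3 = 22% of the target difference. That figure measures exclusion from the analysis, and it would be the same with no replacement at all. It also assumes no comparable loss in the other arm.

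**Nor do the documents establish more drop-out on the tilt table.** Sections 5.3 and 11.1.1 expect less syncope on the Erigo. However, section 10 continues therapy at a lower angle after a blood pressure fall or presyncope, so such an event need not end participation.

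**Conclusion.** The point holds in limited form. As written, the replacement rule applies to the RCT, makes the arm of each substitute known before enrolment, and contradicts the secrecy statement in the sentence before it. At the protocol's own 10% drop-out this concerns about 5 allocations against 50 planned. It can also disturb the stratified allocation, by an amount that depends on a stratum mix the protocol does not give. It conflicts with section 6.2.2, where 50 patients already cover the expected loss; replacement would take enrolment to about 55 or 56.

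These conclusions rest on reading the cross-reference to the pilot literally and on the stated drop-out rate. If replaced patients were also left out of the analysis, which the protocol does not state, the comparison would be restricted to completers. The size and direction of that bias cannot be derived from the document. The defect should be corrected in the protocol because it lies in the allocation itself.

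**What to change.** In section 6.1, under the RCT, state that the substitution rule does not apply, that a drop-out keeps the randomisation number and arm, and that each new patient receives the next concealed allocation in his or her own stratum.

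In section 6.2.2, keep 25 per group as the only allowance for drop-out. Replace the log-book sentence with a statement that randomised patients are analysed in the arm allocated, and that those who stop therapy are still assessed with the CRS-R at weeks 3 and 6 unless the legal proxy withdraws consent to assessment.

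The cost is wording only. Some patients will have incomplete outcome data, particularly where the proxy withdraws consent to assessment. At the planned 10% the existing allowance covers the loss in numbers. How missing values are handled can be left to the statistical analysis plan.
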